## Withdrawal of Subjects from the Study

A subject may be withdrawn from the study at any time if the subject, the investigator, or the Sponsor feels that it is not in the subject’s best interest to continue.

All subjects are free to withdraw from participation at any time, for any reason, specified or unspecified, and without prejudice.

Reasonable attempts will be made by the investigator to provide a reason for subject withdrawals.  The reason for the subject’s withdrawal from the study will be specified in the subject’s source documents.  As noted above, subjects who discontinue study treatment early (i.e., they withdraw prior to Visit 2) should have an early discontinuation visit. Refer to Section 10 for early termination procedures.  Subjects who withdraw after Visit 2 but prior to Visit 3 should be encouraged to come in for a final visit (and the procedures to be followed would include those for their next scheduled visit).

## Replacement of Subjects

Subjects who withdraw from the study treatment will not be replaced.

Subjects who withdraw from the study will not be replaced.

# PRotocol Violations

A protocol violation occurs when the subject, investigator, or Sponsor fails to adhere to significant protocol requirements affecting the inclusion, exclusion, subject safety and primary endpoint criteria. Protocol violations for this study include, but are not limited to, the following:

- Failure to meet inclusion/exclusion criteria
- Use of a prohibited concomitant medication

Failure to comply with Good Clinical Practice (GCP) guidelines will also result in a protocol violation. The Sponsor will determine if a protocol violation will result in withdrawal of a subject.

When a protocol violation occurs, it will be discussed with the investigator and a Protocol Violation Form detailing the violation will be generated. This form will be signed by a Sponsor representative and the Investigator. A copy of the form will be filed in the site’s regulatory binder and in the Sponsor’s files.

# DATA SAFETY MONITORING

The Second Affiliated Hospital of Chongqing Medical University Data Safety Monitoring Board (DSMB) will establish a Data Monitoring Committee (DMC) to review data relating to safety and efficacy, to conduct and review interim analyses, and to ensure the continued scientific validity and merit of the study, according to the Second Affiliated Hospital of Chongqing Medical University Data Safety Monitoring Board Operations Manual and a DMC Charter to be established for this protocol. There will be (number of reviews, if any) interim review(s) conducted by the DMC for the purpose of monitoring study conduct and assessing patient safety. Further details regarding the timing and content of the interim reviews is included in the statistical section below.

# STATISTICAL METHODS AND CONSIDERATIONS

Prior to the analysis of the final study data, a detailed Statistical Analysis Plan (SAP) will be written describing all analyses that will be performed. The SAP will contain any modifications to the analysis plan described below.

## Data Sets Analyzed

All eligible patients who are randomized into the study and receive at least one dose of the study drug (the Safety Population) will be included in the safety analysis.

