# STUDY DESIGN

## Study Overview

This is a cross-sectional study. 304 of subjects are enrolled and applied with biochemical tests, OGTT, and EHC tests on admission. In the subgroup, each subject will be administered lira at the dose of 1.8mg, once a day, and evaluations will be taken before treatment, 12 and 24 weeks after treatment.

Screening data will be reviewed to determine subject eligibility. Subjects who meet all inclusion criteria and none of the exclusion criteria will be entered into the study.

The following treatment regimens will be used:

- Experimental treatment Lira at the following doses: increased from 0.6 mg to 1.8 mg

Total duration of the study is expected to be 24 weeks.

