# SUBJECT SELECTION

## Study Population

Subjects with a diagnosis of IGT and IR who meet the inclusion and exclusion criteria will be eligible for participation in this study.

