# STUDY TREATMENTS

## Method of Assigning Subjects to Treatment Groups

A total of 26 overweight / obese women with IR participated in GLP-1RA intervention for 24 weeks. Included age of 18-35 and BMI of 25-35 kg/m2.

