# EVALUATIONS BY VISIT

## Visit 1 (0 Week)

1. Review the study with the subject (subject’s legal representative) and obtain written informed consent and approved by the ethics committee of the Second Affiliated Hospital of Chongqing Medical University .
2. Assign the subject a unique screening number.
3. Record demographics data.
4. Record medical history,, and prior treatments.
5. Record concomitant medications.
6. Perform a complete physical examination.
7. Perform and record vital signs.
8. Perform and record results of blood pressure testing.
9. Collect blood for clinical laboratory tests (TC, TG, HDL-C, LDL-C, FFA, HbA1c, FBG, 2h-BG, FIns, 2h- INS).
10. Schedule subject for Visit 2 after 12 weeks.
11. List all additional procedures, such as Randomize subject, Dispense study drug, Initiate subject diary, etc.

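### Section 15.1 makes the Safety Population depend on randomization, which the liraglutide part does not have, and on eligibility, which a safety set does not need

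*Protocol*

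**What the plan says.** Data Sets Analyzed (Section 15.1) contains a single rule, the only analysis set that the protocol defines: "All eligible patients who are randomized into the study and receive at least one dose of the study drug (the Safety Population". A patient must therefore be eligible, be randomized, and have been dosed.

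The rest of the protocol describes the treated group as follows:

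- Study Overview calls the study cross-sectional and says of the treated part: "In the subgroup, each subject will be administered lira at the dose of 1.8mg, once a day".
- Method of Assigning Subjects to Treatment Groups names no comparator, ratio or allocation procedure. It says: "A total of 26 overweight / obese women with IR participated in GLP-1RA intervention for 24 weeks".
- The section on drug supply that also describes enrolment gives a clinical reason for entering the liraglutide group (ovarian and menstrual problems) and says that 26 women were followed to the end.
- The paragraph on numbers under Interim Analysis plans 30 women for liraglutide.
- The only other mention of randomization is a template prompt at Visit 1: "List all additional procedures, such as Randomize subject, Dispense study drug, Initiate subject diary, etc".

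On eligibility, Study Overview says "Screening data will be reviewed to determine subject eligibility" and then "Subjects who meet all inclusion criteria and none of the exclusion criteria will be entered into the study". Study Population says "Subjects with a diagnosis of IGT and IR who meet the inclusion and exclusion criteria will be eligible for participation in this study". The section on protocol violations lists "Failure to meet inclusion/exclusion criteria" as a violation and leaves it to the Sponsor whether the subject is withdrawn.

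**The concern.** A safety set should follow exposure: anyone who received the drug was at risk from it. Section 15.1 adds two further conditions, and each fails in its own way.

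The first, *randomized*, describes something that does not happen in this study, so the definition cannot be applied as written. The second, *eligible*, is compatible with a single treated group but has two possible meanings. Under one of them, a woman who received liraglutide and was later found not to meet the criteria drops out of the safety summary.

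At stake is the summary of safety and tolerability promised under Analysis of Secondary Endpoints, together with the named secondary endpoint, serious adverse events within 24 weeks. In a group this small each woman carries noticeable weight. The set should not depend on a reading chosen after events are known.

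**Working it through.** The protocol gives no figure to reproduce here. The check compares the definition with the design and counts who would be in the set under each reading.

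**Inputs**

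- Conditions for membership: eligible, randomized, dosed (Data Sets Analyzed).
- Number randomized: none described (Study Overview; Method of Assigning Subjects to Treatment Groups).
- Number dosed, *N*: not stated. At least 26, because 26 were followed to the end. If the planned 30 were all dosed, *N* = 30. The difference, 30 − 26 = 4, could be dosed women who stopped early or places never filled; the protocol does not say. The range 26 to 30 is therefore an assumption.
- Number of dosed women later found in breach, *v*: not stated.

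**Step 1: *randomized*.** Both the design section and the assignment section describe one group in which everybody receives liraglutide, and entry was for a clinical reason. The Visit 1 prompt is an unfilled example with no arms, ratio or method behind it. Applied literally, the condition is met by nobody, so the set has 0 members whatever *N* is.

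**Step 2: *eligible*, with *randomized* set aside.**

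- Status judged at entry: everyone admitted after screening counts as eligible. Set size = *N*; nothing is lost.
- Actual fulfilment of all criteria: set size = *N* − *v*.

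Study Overview supports the entry reading, because screening data are used to decide who enters. Study Overview and Study Population also tie eligibility to meeting the criteria, which supports the stricter reading. Section 15.1 does not choose between them.

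**Step 3: how much one exclusion could matter.** Suppose, for illustration only, *v* = 1, and let *x* of the *N* dosed women have an event.

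- If the violator had an event, the rate falls by *x*/*N* − (*x* − 1)/(*N* − 1) = (*N* − *x*)/[*N*(*N* − 1)]. This is largest at *x* = 1, where it equals 1/*N*.
- If she had none, the rate rises by *x*/(*N* − 1) − *x*/*N* = *x*/[*N*(*N* − 1)]. This also cannot exceed 1/*N*, since *x* is at most *N* − 1.

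So one exclusion moves a rate by at most 1/26 = 3.8 percentage points, or 1/30 = 3.3 points, in either direction. It is usually less: with five events among 26, none of them in the violator, the change is from 5/26 = 19.2% to 5/25 = 20.0%, or 0.8 points.

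**Step 4: what is not affected.** Adverse events are captured throughout the study. All SAEs are documented from consent to the final visit and go to the ethics committee regardless of causality. The Synopsis has the monitoring committee follow SAEs continuously. None of these steps is restricted to the Safety Population. The primary objective, the association of serum Fetuin-B with IR and IGT, does not use this set.

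**The case against.** The strongest reply is that *randomized* is leftover template wording. The protocol has other such traces: an unfilled placeholder for the number of interim reviews, and a baseline summary by dose level. With one treated group, *entered and dosed* is the only workable meaning, and no analyst would report an empty safety set. That stands. A reader might infer that the safety analysis would really be run on 0 of 26 women, and the documents do not support that. The empty set shows that the sentence is wrong; it is not a forecast of the report.

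On *eligible*, the reply is that status at entry is the more natural meaning and costs nothing, that the violations section concerns withdrawal rather than analysis sets, and that no dosed violator is reported or predicted. This also stands as far as it goes. It does not remove the ambiguity, because the protocol itself foresees breaches of the entry criteria and Section 15.1 is silent on how they are handled.

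Finally, the opening of the statistical section promises a SAP that will contain any modifications. That is a route to repair. It does not correct the text, and this is a definition that the protocol has already fixed rather than a detail left open.

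**Conclusion.** The definition is wrong as written and should be changed; the practical effect is probably small. That *randomized* contradicts the design is clear from the protocol alone. That *eligible* could exclude an exposed woman holds only under the stricter reading and only if such a woman exists. Under the entry reading nothing is lost.

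The numerical effect is unknown, because neither the number dosed nor the number in breach is given. The bound of 3.3 to 3.8 percentage points per excluded woman assumes 26 to 30 dosed and a single violator. It shows scale and is not an estimate.

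Two stronger inferences are not supported. One is that safety information would be lost: collection, reporting and committee review are not filtered, so only the descriptive summaries are touched. The other is that 26 is the number treated. The assignment section says that 26 took part, but the same figure is given for those followed to the end, and 30 were planned, so 26 may be completers only.

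**What to change.** In Section 15.1, define the Safety Population as every subject given one or more doses of liraglutide, and delete both *eligible* and *randomized*. Replacing *randomized* with *enrolled* would not be enough, because the eligibility condition would remain. The exposure-only wording also makes plain that dosed women who did not complete 24 weeks belong in the denominator. List women found to breach the entry criteria, with their adverse events, separately, and state the number dosed.

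The cost is one sentence in the protocol, carried into the SAP, with no new data. The only consequence is that the reported event rate may shift slightly, up or down, compared with a set that excludes violators.

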## Demographic and Baseline Characteristics

The following demographic variables at screening will be summarized by dose level: gender, age, BP, WC, Fat %, height and weight.

## Analysis of Primary Endpoint

After application of lira, Physical examination and biochemical tests, OGTT, and EHC tests were performed before treatment, 12 and 24 weeks after treatment.

## Analysis of Secondary Endpoints

If the subjects had serious adverse events within 24 weeks, the application of lira would be stopped. Safety and tolerability data will be summarized by treatment group.

## Interim Analysis

All of the subjects were asked to come back to the outpatient to receive physical examination and biochemical tests, OGTT, and EHC tests at 12 week to assess the effect of lira.

The sample size for this protocol was determined by the patients number of the Second Affiliated Hospital of Chongqing Medical University from January 2017 to December 2019. We planed to enroll 300 subjects for cross-sectional study and 30 subjects for lira administration.

# DATA COLLECTION, RETENTION AND MONITORING

## Data Collection Instruments

The Investigator will prepare and maintain adequate and accurate source documents designed to record all observations and other pertinent data for each subject treated with the study drug.

Study personnel at each site will enter data from source documents corresponding to a subject’s visit into the protocol-specific electronic Case Report Form (eCRF) when the information corresponding to that visit is available. Subjects will not be identified by name in the study database or on any study documents to be collected by the Sponsor (or designee), but will be identified by subject number.

For eCRFs: If a correction is required for an eCRF, the time and date stamps track the person entering or updating eCRF data and creates an electronic audit trail.

The Investigator is responsible for all information collected on subjects enrolled in this study. All data collected during the course of this study must be reviewed and verified for completeness and accuracy by the Investigator. A copy of the CRF will remain at the Investigator’s site at the completion of the study.

## Data Management Procedures

The data will be entered into a validated database. The Data Management group will be responsible for data processing, in accordance with procedural documentation. Database lock will occur once quality assurance procedures have been completed.

All procedures for the handling and analysis of data will be conducted using good computing practices meeting CSE guidelines for the handling and analysis of data for clinical trials.

## Data Quality Control and Reporting

After data have been entered into the study database, a system of computerized data validation checks will be implemented and applied to the database on a regular basis. The study database will be updated in accordance with the resolved queries. All changes to the study database will be documented.

## Archival of Data

The database is safeguarded against unauthorized access by established security procedures; appropriate backup copies of the database and related software files will be maintained.  Databases are backed up by the database administrator in conjunction with any updates or changes to the database.

At critical junctures of the protocol (e.g., production of interim reports and final reports), data for analysis is locked and cleaned per established procedures.

## Availability and Retention of Investigational Records

The Investigator must make study data accessible to the monitor, other authorized representatives of the Sponsor (or designee), IRB/IEC, and Regulatory Agency inspectors upon request. A file for each subject must be maintained that includes the signed Informed Consent, Assent Form and copies of all source documentation related to that subject. The Investigator must ensure the reliability and availability of source documents from which the information on the CRF was derived.

All study documents (patient files, signed informed consent forms, copies of CRFs, Study File Notebook, etc.) must be kept secured for a period of two years following marketing of the investigational product or for two years after centers have been notified that the IND has been discontinued. There may be other circumstances for which the Sponsor is required to maintain study records and, therefore, the Sponsor should be contacted prior to removing study records for any reason.

## Monitoring

Monitoring visits will be conducted by representatives of the Sponsor according to the the ethics committee of the Second Affiliated Hospital of Chongqing Medical University. By signing this protocol, the Investigator grants permission to the Sponsor (or designee), and appropriate regulatory authorities to conduct on-site monitoring and/or auditing of all appropriate study documentation.

## Subject Confidentiality

In order to maintain subject confidentiality, only a subject number will identify all study subjects on CRFs and other documentation submitted to the Sponsor. Additional subject confidentiality issues are covered in the Clinical Study Agreement.

# ADMINISTRATIVE, ETHICAL, REGULATORY CONSIDERATIONS

The study will be conducted according to the Declaration of Helsinki,and approved by the ethics committee of the Second Affiliated Hospital of Chongqing Medical University (2014 Colombo Review No. (72)).

To maintain confidentiality, all laboratory specimens, evaluation forms, reports and other records will be identified by a coded number and initials only. All study records will be kept in a locked file cabinet and code sheets linking a patient’s name to a patient identification number will be stored separately in another locked file cabinet. Clinical information will not be released without written permission of the subject.

## Protocol Amendments

Any amendment to the protocol will be written by [name]. Protocol amendments cannot be implemented without prior written IRB/IEC approval except as necessary to eliminate immediate safety hazards to patients. A protocol amendment intended to eliminate an apparent immediate hazard to patients may be implemented immediately, provided the IRBs are notified within five working days.

## Institutional Review Boards and Independent Ethics Committees

The protocol and consent form will be reviewed and approved by the IRB/IEC of each participating center prior to study initiation. Serious adverse experiences regardless of causality will be reported to the IRB/IEC in accordance with the standard operating procedures and policies of the IRB/IEC, and the Investigator will keep the IRB/IEC informed as to the progress of the study. The Investigator will obtain assurance of IRB/IEC compliance with regulations.

Any documents that the IRB/IEC may need to fulfill its responsibilities (such as protocol, protocol amendments, Investigator’s Brochure, consent forms, information concerning patient recruitment, payment or compensation procedures, or other pertinent information) will be submitted to the IRB/IEC. The IRB/IECs written unconditional approval of the study protocol and the informed consent form will be in the possession of the Investigator before the study is initiated. The IRB/IECs unconditional approval statement will be transmitted by the Investigator to the Sponsor prior to the shipment of study supplies to the site. This approval must refer to the study by exact protocol title and number and should identify the documents reviewed and the date of review.

Protocol and/or informed consent modifications or changes may not be initiated without prior written IRB/IEC approval except when necessary to eliminate immediate hazards to the patients or when the change(s) involves only logistical or administrative aspects of the study. Such modifications will be submitted to the IRB/IEC and written verification that the modification was submitted and subsequently approved should be obtained.

The IRB/IEC must be informed of revisions to other documents originally submitted for review; serious and/or unexpected adverse experiences occurring during the study in accordance with the standard operating procedures and policies of the IRB; new information that may affect adversely the safety of the patients of the conduct of the study; an annual update and/or request for re-approval; and when the study has been completed.

## Informed Consent Form

Informed consent will be obtained in accordance with the Declaration of Helsinki and the ethics committee of the Second Affiliated Hospital of Chongqing Medical University.

The Investigator will prepare the informed consent form, assent and HIPAA authorization and provide the documents to the Sponsor or designee for approval prior to submission to the IRB/IEC. The consent form generated by the Investigator must be acceptable to the Sponsor and be approved by the IRB/IEC. The written consent document will embody the elements of informed consent as described in the International Conference on Harmonisation and will also comply with local regulations. The Investigator will send an IRB/IEC-approved copy of the Informed Consent Form to the Sponsor (or designee) for the study file.

A properly executed, written, informed consent will be obtained from each subject prior to entering the subject into the trial. Information should be given in both oral and written form and subjects (or their legal representatives) must be given ample opportunity to inquire about details of the study. If appropriate and required by the local IRB/IEC, assent from the subject will also be obtained. If a subject is unable to sign the informed consent form (ICF) and the HIPAA authorization, a legal representative may sign for the subject. A copy of the signed consent form (and assent) will be given to the subject or legal representative of the subject and the original will be maintained with the subject’s records.

## Publications

The preparation and submittal for publication of manuscripts containing the study results shall be in accordance with a process determined by mutual written agreement among the study Sponsor and participating institutions. The publication or presentation of any study results shall comply with all applicable privacy laws, including, but not limited to, the Health Insurance Portability and Accountability Act of 1996.

